### Procedure

After including the patients for participation in the study, they will be divided into an intervention and control group by means of randomization. We have not opted for a crossover design, as it cannot be estimated how long the wash-out period will be [19]. For the sake of the validity of the results to be obtained, a period of six weeks (2 + 2 + 2) has been chosen for the intervention group as well as for the control group. During this total period, both groups of demented patients will continuously wear an actiwatch (respironics type AW2) on the non-dominant wrist. Practice has shown that this watch hardly causes any nuisance or no nuisance at all.

In addition, a daily sleep diary will be kept by the nursing staff for all participants.

In the first two weeks, the baseline situation (T0) of the intervention group and control group will be measured by means of the actiwatch. In the next two weeks, as the intervention is executed in the intervention group, in both groups the actiwatch measurements will be continued (T1). In the last two weeks the wash-out of the intervention will be measured and again in both groups the actiwatch measurements will be continued (T2).

During the whole period, the doors of the bedrooms of all participants in both groups will remain closed during the night, in order to prevent disruptions. Yet, if a patient or staff member enters/leaves the room, this will be noted in the sleep diary.

After the study period of six weeks, the actiwatches will be read out. The collected data per patient will be recorded, together with the other relevant data. These include registered changes in the situation of the patients during the study period, for example (1) possible additional co-morbid illness(es) that may lead to a change in the level of motor restlessness or in the normal day/night pattern of the patient (for example pneumonia, delirium, urinary retention, constipation), or (2) changes in the use of psychotropic drugs, therapies, and/or use of restraints.

A schematic representation of the procedure can be found in Table 1.

**Table 1 T1:** Measurements overview

Moment	T0	Baseline	T1	Baseline	T2	Intervention	T3	Intervention	T4	Wash-out	T5	Wash-out	T6
Week	0	1		2		3		4		5		6	
Actiwatch		Continuous		Continuous	*Charging*	Continuous		Continuous	*Charging*	Continuous		Continuous	
NPI-Q					T2				T4				T6
BANS-S	T0												
Patient characteristics	T0												
Sleep diary		Continuous		Continuous		Continuous		Continuous		Continuous		Continuous	
Status examination			T1		T2		T3		T4		T5		T6

T0, the week previous to the measuring period: complete BANS-S and make an inventory of patient characteristics (CIRS); T1, status examination; T2, end of baseline period: complete NPI-Q and status examination; T3, status examination; T4, end of intervention period: complete NPI-Q and status examination; T5, status examination; T6, end of wash-out period: complete NPI-Q and status examination. Actigraphy is taking place continuously. At T2 and T4, the actiwatch will be charged for a short period (ca. 2 h).

A qualitative status examination will take place weekly (changes in medication, therapy, medical condition, means and measures, restlessness). The sleep diary will be filled in daily during the whole measuring period.

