### Interventions

Patients will be randomized over an intervention group and a control group. The patients in the control group will sleep on their own high-dependency bed during the three periods of two weeks each. The patients in the intervention group will sleep, after the initial baseline period of two weeks, on a high dependency bed identical to their own for the second period of two weeks. The mattress of this bed, however, contains the same technique as the PAS therapy chair and will be controlled by an external computer. As the intervention can be controlled perfectly and safely via the computer regarding frequency, duration and intensity, the technique is considered suitable for this research. In the third and last (wash-out) period of two weeks they sleep again in their own bed.

The computer programme controlling the acoustic vibrations of the mattress will be switched on daily by the nursing staff during a period of two weeks. This will be done as soon as the patient is lying in bed. The programme will switch off automatically after 30 min. So as to not contaminate the results by the presence of the staff, the staff member will leave the patient's bedroom as soon as the mattress is switched on. The frequencies used in the programme lie between 27 and 40 Hz and will vary every two or three minutes.

These frequency settings of the intervention have been chosen after advice from Finnish professionals who have many years of experience with this intervention. The design of the programme used in this intervention was originally aimed at reducing pain, and the varying frequencies were based on Melzak and Wall's gate control theory [17].

The other therapeutic applications of PAS therapy described above, whose effectiveness has already been proven, are all based on this design as well.

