### Randomization

By means of blinded block randomization with group sizes of six, the randomization scheme will determine which patients will be placed in the intervention group and the control group. The intervention is not blinded because it is visible for the caregiver (box with computer below the bed and faintly audible (a very low buzz).

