### Primary outcome measures

The objectively and subjectively measured difference in nocturnal restlessness between T0-T1-T2. Objectively, the nocturnal restlessness measured during six weeks by means of an actiwatch validated for sleep research with the sleep/wake parameters mentioned above.

Subjectively, nocturnal restlessness determined on the basis of a sleep diary developed for this study, and filled in by the nursing staff.

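### Patients are randomised before the two-week baseline although the arms do not differ until week 3; allocation, or its release to the ward, should wait until the end of week 2

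*Protocol article*

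**What the plan says.** T0, T1 and T2 are used here as in the text of the Procedure and Statistical analysis sections: baseline, intervention and wash-out periods. Table 1 uses the same labels differently.

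- **Order of events (Procedure).** "After including the patients for participation in the study, they will be divided into an intervention and control group by means of randomization". The measurement periods follow, beginning with: "In the first two weeks, the baseline situation (T0) of the intervention group and control group will be measured by means of the actiwatch".
- **When the arms diverge (Interventions).** "The patients in the intervention group will sleep, after the initial baseline period of two weeks, on a high dependency bed identical to their own". Until then both arms are in their own beds.
- **Blinding (Randomization).** "The intervention is not blinded because it is visible for the caregiver". The reasons given are the computer box and a faint buzz.
- **Sequence (Randomization).** "By means of blinded block randomization with group sizes of six". What is blinded about it is not explained.
- **Who records.** According to the Procedure section, "a daily sleep diary will be kept by the nursing staff for all participants", so from week 1. The NPI (NPI-Q in Table 1, NPI-NH in Data collection) is first completed at the end of week 2, by a psychologist with a nurse who knows the patient.
- **Role of these measures.** Primary outcome measures has an actigraphic part and a diary part: "Subjectively, nocturnal restlessness determined on the basis of a sleep diary developed for this study, and filled in by the nursing staff". The NPI serves the secondary outcome. Statistical analysis puts actigraphy and NPI-NH into a mixed model over T0, T1 and T2, reads the therapy effect from T0-T1, and analyses the diary separately by descriptive statistics.

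**The concern.** A baseline is safest when nobody who records it, or who cares for the patient, can know the arm. Here the stated order gives that protection up with no visible gain, because no treatment difference needs the arm to be known before week 3.

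If ward staff do know the arm in weeks 1-2, three routes are open. The nurse's contribution to the week-2 NPI-NH may differ by arm. So may the diary. Actigraphy is not scored by staff, so it could move only through changed care, such as room entries or changes in medication. Expectation is plausible, since the Background says that the nursing home's own staff came upon this use of the treatment. Because the effect is a change from T0, a disturbed baseline disturbs the effect. The direction is open: higher restlessness recorded at baseline in the intervention arm would flatter PAS, and lower would hide a benefit.

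A second, smaller consequence is that a patient who leaves in weeks 1-2 is a randomised loss with no T1 value.

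**Working it through.** **1. The plan's own figure.** Sample size gives 80% against 50%, alpha 5%, power 80%, drop-out 10%, total 66. With a one-sided test and unpooled variance: n = (1.645 + 0.842)² × (0.8×0.2 + 0.5×0.5) / 0.30² = 28.2, so 29 per arm; 29/0.9 = 32.2, so 33 per arm and 66 in total. The same formula two-sided gives 36 per arm and 80 in total. The test's sidedness is not stated and is a separate matter. What counts here is that the date of allocation is not an input, so moving it leaves this calculation unchanged.

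**2. Numbers under later allocation.** With 66 enrolled and 10% drop-out, completers are 66 × 0.9 = 59.4 under either timing. The document does not say when drop-out occurs. Assume a share s of it (on the log scale) falls in weeks 1-2; the number reaching allocation is then 66 × 0.9^s, and the enrolment needed to randomise 66 is 66/0.9^s.

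| Share in weeks 1-2 (assumed) | Randomised from 66 enrolled | Completers | Enrolment needed to randomise 66 |
|---|---|---|---|
| none | 66.0 | 59.4 | 66 |
| one third | 63.7 | 59.4 | 69 |
| half | 62.6 | 59.4 | 70 |
| all | 59.4 | 59.4 | 74 |

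**3. How a baseline shift carries through.** Suppose recording or care shifts the baseline of one arm by b SD and leaves follow-up unaffected. A difference in change from T0 is then biased by the full b. A comparison adjusted for baseline is biased by ρ×b, where ρ is the baseline to follow-up correlation.

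For an illustration, assume SD 1, one baseline and one follow-up value, 30 per arm (33 × 0.9 = 29.7), a two-sided 5% test and b = 0.2. The standard errors are √(2(1-ρ)) × √(2/30) for change and √(1-ρ²) × √(2/30) with adjustment. For ρ = 0.5 the change-score standard error is 0.258, the shift is 0.2/0.258 = 0.77 standard errors, and the rejection rate with no true effect is 12%.

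| ρ (assumed) | Change score | Baseline-adjusted |
|---|---|---|
| 0.5 | 12% | 7% |
| 0.7 | 17% | 12% |
| 0.8 | 23% | 18% |

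With b = 0.1 the ranges are 7-9% and 6-8%; with b = 0 all are 5%. None of b, ρ or the SD comes from the document.

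**4. Block size.** For a 3:3 block of six, the expected number of allocations already determined by earlier ones is 2×3/(3+1) = 1.5 of 6. The best guess is right in 3 + (2⁶/20 - 1)/2 = 4.1 of 6, or 68%. Enumerating all 20 arrangements gives the same values. Both assume that someone knows the block size and sees every earlier allocation in the sequence.

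**The case against.** The strongest reply is that knowledge of the arm during baseline is inferred. The stated reason for non-blinding is the visible and audible equipment, which is absent until week 3. The randomisation is called blinded, which may mean concealed. An article may leave the date of disclosure to the full protocol, and if the ward learns the arm only at the bed exchange, the risk is already small. This stands in part: a reader might infer that staff do know the arm in weeks 1-2, and the article does not say so. It does state the order of events, though, and that order is what can be improved.

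Other replies also hold:

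- The diary is only described and the NPI is secondary. The modelled primary measure is actigraphy, which staff could affect only through care. No evidence of such a change is given.
- A reader might infer that losses before treatment dilute the effect. They do not. Dilution needs untreated patients who contribute follow-up, whereas early leavers contribute T0 data and no T1 value.
- A reader might take an assumed shift, or a ratio of it to some detectable standardised difference, as the size of the bias. The plan is sized on 80% against 50% and gives no SD.
- The 68% is a worst case. Patients come from five wards, and nothing says that any one person sees the whole sequence.
- The number of PAS beds is not given, so scheduling them may be a reason to allocate early.

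**Conclusion.** The point holds at modest size. As described, the baseline is collected after randomisation in a trial open to caregivers, with no stated safeguard, although treatment does not differ until week 3. Whether this causes bias depends on an unstated fact (when the ward learns the arm) and on a shift of unknown size and direction. If there is a shift, it enters a T0-T1 change comparison in full and a baseline-adjusted one in proportion to ρ. The NPI-NH is the most exposed of the modelled outcomes and actigraphy the least; for the diary the effect would be on a descriptive comparison. The error rates above show how sensitive the contrast is and do not estimate what will happen in this trial. Early losses cost precision only. The document does not support saying that the baseline is biased or that the effect will be diluted.

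**What to change.** Trial status says that recruitment is still under way, so a procedural amendment can apply to patients not yet randomised.

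- **Preferred.** Carry out the allocation only after a patient's baseline actiwatch period and week-2 NPI-NH are complete. Table 1 already has a contact at that point, when the watch is charged. Report earlier losses as pre-randomisation.
- **Minimum.** Keep the present date of allocation but release it, concealed until then, at the same point, and say so. Early leavers would then still count as randomised, but their leaving could not depend on knowledge of the arm. If this is already the practice, one sentence settles the matter.
- **Optional.** Vary the block size at random and do not disclose it. Later allocation does not by itself prevent guessing from fixed blocks of six.

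**Cost.** A PAS bed must be available at short notice at the start of week 3. With the preferred change, slightly fewer than 66 may be randomised from 66 enrolled, with the same expected completers; keeping 66 randomised would take 69 to 74 enrolled if a third or more of the drop-out falls in baseline. Patients before and after the amendment will have been allocated at different times, which the report should state. Unblinded recording in weeks 3-6 is not addressed by this change.

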### Data collection

First, the following patient characteristics will be collected for both groups: age, gender, type of dementia, co-morbidity (by means of CIRS [20]), incontinence Yes or No, the use of restraints (for example fixation belts), medication (including psychopharmacological drugs), and other therapies.

In addition, the Bedford Alzheimer Nursing Severity Scale (BANS-S) [21] will be applied by the psychologist together with the nursing staff to get an impression of the severity of dementia. This validated scale contains seven items to assess functional and cognitive capacities as well as pathological symptoms. These items, scaled 1 to 4, are summed. The overall score ranges from 7 (no impairment) to 28 (complete impairment).

Although the traditional 'gold standard' assessing the quality of the sleep is polysomnography (PSG), it is difficult to apply PSG to patients with a moderate to serious form of dementia [22,23]. Therefore, in studies like this, often more feasible assessment methods are used, like observation-oriented techniques and actigraphy. Actigraphy is a less invasive method than PSG, offering a reliable way to estimate sleep/wake parameters including nocturnal restlessness [24]. In this study we will use both actigraphy and sleep diaries.

The nocturnal restlessness will be measured by validated actigraphy [25-27] in the intervention group as well as in the control group on the basis of the following sleep/wake parameters [28,29]: (1) nocturnal restlessness: average motor activity during the night; (2) sleep efficiency: the number of hours the patient is lying in bed and actually sleeping; (3) wake bouts: the number of episodes the patient is awake during the night; (4) inter-daily stability: the degree of stability in activity patterns over longer periods of time; (5) intra-daily variability: the degree of inconstancy in rest and activity during a day [28,29].

When considering nocturnal restlessness it is important to take measurements during a period of at least two weeks. In this way, the statistic power will increase [30].

To determine the degree to which the actimeters respond to the acoustic vibrations of the mattress themselves, a control actimeter is placed on the mattress in advance.

In addition, other relevant sleep observation data of every patient will be written down in a sleep diary, in which nocturnal restlessness and the day/night rhythm, as observed by the nursing staff will be recorded.

As shown in previous research, this 'subjective' information will optimize the 'objective' information gained by using the actimeters [31]. The nursing staff will receive instructions on how to use the actiwatch, how to fill in the sleep diary, and how to operate the computer.

Finally, it is important to carefully monitor the changes in behavior of the participating demented residents, over the total study period. Therefore, a validated Neuropsychiatric Inventory assessment (NPI-NH) [32] will be performed in weeks 2, 4, and 6 by a psychologist together with a nursing staff member who knows the patient well. The NPI-NH contains 10 behavioral aspects and two types of neuro-vegetative changes, that is delusions, hallucinations, agitation, depression/dysphoria, anxiety, euphoria/elation, apathy/indifference, disinhibition, irritability/lability, aberrant motor behavior, night-time disturbances, and appetite/eating change. This inventory will provide information on possible coexisting neuropsychiatric symptoms in patients with Alzheimer disease or other dementia syndromes.

Both the frequency and severity of each symptom are rated on a four- (1-4) and three-point (1-3) Likert scale, respectively. A separate score can be calculated for each symptom by multiplying the frequency and severity scores, results ranging from 0 to 12 for each symptom. A total score can be obtained by summing the 12 frequency and severity scores, yielding total scores that range from 0 to 144 [33].

### Adverse effects

The study will be terminated if (1) the patient resists by verbally and/or non-verbally putting up resistance when using the intervention mattress and/or the actiwatch to a higher degree than usual in situations deviating from the daily routine; and (2) one of the previously mentioned exclusion criteria is met during the intervention period.

As demented residents often cannot express their own will themselves, the legal representative (mostly a family member), together with the nursing staff, nursing home physician, and/or psychologist, will assess whether resistance to the intervention applies to the patient.

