### Approval

This study follows the Dutch Medical Research Involving Human Subjects Act's (WMO) and the Helsinki Declaration's principles, meaning that the (legal) representatives of all demented patients will sign a written informed consent, stating also that participation can be withdrawn at any time, whenever the patient shows resistance, without any negative consequences concerning their current or future medical treatment. The Medical Ethical Committee of Maastricht University has granted ethical approval (protocol 2011 nr. NL35287.068.11).

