### Statistical analysis

In order to process the data to test our hypothesis, the statistical software programme SPSS-19 [34] will be used. First, data will be checked for missing values and normal distribution. It will be examined whether there is a significant difference in both nocturnal restlessness and degree of neuropsychiatric symptoms between the intervention group and the control group.

To analyze the actigraphy variables and the variables measured by means of NPI-NH (T0, T1, and T2) integrally, a multilevel regression model (Mixed Models) will be used. In this study, the Basic Two-Level Regression Model [35] will be used, in which the actigraphy variables and NPI-NH variables are the lowest levels (that is dependent variable) and the research participants the highest level (independent variable).

The multilevel analysis enables us to calculate the degree of nocturnal restlessness and neuropsychiatric symptoms despite the unequal number of observations per individual (missing values/dropouts). This means that all data will be included in the analysis, including the data of participants who will meet stop criteria during the investigation and for whom the study has to be terminated early.

If there is interaction effect between time and group, a post-hoc analysis will be performed, taking into account that T0-T1 indicates PAS therapy effects and that T1-T2 indicates the long-term effects of PAS therapy. The analyses will be corrected for basic differences in the characteristics of the patients belonging to the intervention group and the control group respectively. The data in the sleep diaries will first be coded and later analyzed separately by means of describing statistics.

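### Resisting the PAS mattress ends measurement as well as treatment, so follow-up is lost by a route that exists only in the PAS arm

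*Protocol article*

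**What the plan says.** Four sections of the protocol article bear on this.

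- **Adverse effects.** The study is ended if "the patient resists by verbally and/or non-verbally putting up resistance when using the intervention mattress and/or the actiwatch", so the rule covers resistance to either. Meeting an exclusion criterion during the intervention period is listed as item (2).
- **Statistical analysis.** The stop applies to the individual and to the study as a whole: these are participants "for whom the study has to be terminated early". The section groups them with missing values and drop-outs, and it says that "all data will be included in the analysis, including the data of participants who will meet stop criteria during the investigation".
- **Approval.** The consent form states that "participation can be withdrawn at any time, whenever the patient shows resistance".
- **Interventions and Procedure.** "The patients in the control group will sleep on their own high-dependency bed during the three periods of two weeks each", whereas "both groups of demented patients will continuously wear an actiwatch".

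No section provides for stopping the mattress while measurement goes on. Keeping all data in the analysis covers what was collected before the stop. It does not say that anything is collected afterwards.

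**The concern.** One event, refusing the mattress, ends two things that need not end together: exposure to PAS and observation of the outcome. A control patient cannot refuse a mattress that he or she is never given, so this cause of missing data is confined to the PAS arm.

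It may also be related to the outcome. The Background describes nocturnal restlessness as motor and/or verbal behaviour, and the stop rule looks for verbal or non-verbal resistance at the time the mattress is used. The two could overlap, although the document does not say that they do.

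What is at stake is the comparison of everyone randomised. If patients who do not tolerate the mattress vanish from follow-up, the later results in the PAS arm describe mainly those who do. No analysis plan can recover ratings that were never made.

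**Working it through.** **1. Plan figures.** The plan gives no expected rate of resistance. The nearest figure is the single 10% drop-out allowance in the Sample size section, not split by arm: 0.10 × 33 = 3.3 patients per arm. The total of 66 can be reproduced with a one-sided arcsine formula for 80% versus 50% at 80% power (29.9, so 30 per arm; 30 × 1.1 = 33; 2 × 33 = 66). This point does not depend on it.

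**2. What a mattress stop removes.** Each two-week period has 14 nights, 42 in all, and the mattress is used only in weeks 3 and 4. A patient who stops after m nights on it keeps 14 + m nights and loses (14 − m) + 14 = 28 − m. With m = 3 as an example:

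| Data | Planned | Kept | Lost |
|---|---|---|---|
| Actigraphy and diary, baseline nights | 14 | 14 | 0 |
| Actigraphy and diary, intervention nights | 14 | 3 | 11 |
| Actigraphy and diary, wash-out nights | 14 | 0 | 14 |
| NPI-NH ratings (weeks 2, 4, 6) | 3 | 1 | 2 |

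That is 25 of 42 nights (60%). Whatever m is, all wash-out nights go. Because the mattress is used only between the week-2 and week-4 ratings, a patient stopped before the week-4 rating has only the baseline NPI-NH.

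**3. Diary.** The Statistical analysis section has the diary coded and described separately, so no model compensates for missing nights. As an illustration, suppose the true restlessness rate is 80% in both arms, k of 33 PAS patients leave, all of them restless, and they drop out of the summary. The apparent PAS rate is (0.80 × 33 − k) / (33 − k):

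| k (assumed) | Calculation | Apparent PAS rate | Spurious difference |
|---|---|---|---|
| 1 | 25.4 / 32 | 79.4% | 0.6 points |
| 3 | 23.4 / 30 | 78.0% | 2.0 points |
| 5 | 21.4 / 28 | 76.4% | 3.6 points |
| 7 | 19.4 / 26 | 74.6% | 5.4 points |

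The planned difference is 30 points. The direction follows from assuming that every leaver is restless. If leavers were restless at the same 80% as the rest, the difference would be zero.

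**4. Actigraphy.** All simulation inputs are assumptions: between-patient SD 1, night-to-night SD 1, period-response SD 0.5, 33 per arm, stop after three mattress nights.

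- *No true effect, and the 3 or 5 PAS patients with the largest early rise stop.* A precision-weighted comparison of change scores shifts by about 0.09 or 0.13 SD towards PAS if these patients are dropped altogether. If their pre-stop nights are kept and the stop depends only on those nights, the shift is about 0.
- *5 of 33 are 1 SD worse on the mattress and would return to baseline in their own bed; random-intercept model.* Compared with full follow-up, stopping measurement shifts T1 by about 0.03 SD against PAS with no benefit in those who tolerate the mattress, and by about 0.02 SD towards PAS with a 0.5 SD benefit. At T2 the shift is 0.03 to 0.05 SD against PAS.
- *3 to 7 stop, with a 0.64 SD benefit in those who tolerate it.* The shift is 0.03 to 0.04 SD towards PAS with a random intercept, and 0.02 to 0.07 SD against PAS with patient-specific slopes.

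With pre-stop nights kept, the shifts are small and their sign changes with the model and with the true effect.

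**The case against.** The strongest defence is that the plan already limits the damage. Pre-stop nights stay in a multilevel model, and those nights include the ones on which the patient resisted, which count against PAS. The unseen nights would be spent in the patient's own bed, where a return towards baseline is at least as plausible as continued worsening. This stands for actigraphy, as long as missing at random is a fair description.

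Three stronger readings are tempting, and the documents do not support them.

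- *That the whole stop rule works in one arm only.* It does not. The same sentence covers the actiwatch, which both arms wear, and the exclusion criteria are not tied to the mattress. Only the mattress trigger is one-sided.
- *That resisters are the patients who became more restless.* This is a reasonable inference from two overlapping descriptions of behaviour, but no section says that resisters have worse actigraphy.
- *That the estimate therefore leans towards PAS by a calculable amount.* Any such figure multiplies an assumed share of stoppers by an assumed shift in their unseen nights. The documents give neither, and the simulations show both signs.

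A further objection concerns consent. The Approval section links resistance to withdrawal from participation, for patients who often cannot speak for themselves. Continued measurement is therefore more than an administrative matter. This also stands, and it shapes the fix.

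**Conclusion.** The point holds as a weakness of design. As written, resisting the mattress ends outcome collection, and that trigger can arise only in the PAS arm. Follow-up is therefore lost differentially, for reasons that may be related to restlessness.

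For actigraphy, the size and sign of any bias are unknown. It is probably small, given that pre-stop nights are kept and that missing at random is roughly right.

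The exposure is greater in three places:

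- the NPI-NH, where a patient stopped before week 4 has no rating after baseline, so the model can only borrow from patients who tolerated the mattress;
- the sleep diary, a primary outcome with descriptive analysis only, where the illustration gives 0.6 to 5.4 points for one to seven restless leavers;
- the wash-out contrast (T1-T2), to which these patients contribute no wash-out nights.

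The document gives no rate of resistance, so these sizes are illustrations and not estimates. The change is worth making because it is cheap and the lost data cannot be recovered later. The point does not by itself invalidate the trial.

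**What to change.** Leave the mattress stop rule as it is and separate it from data collection. State that, when only the mattress is stopped, actiwatch, sleep diary and NPI-NH continue to week 6 in the patient's own bed, unless the patient resists the watch or the representative withdraws consent. Analyse these patients in the arm to which they were randomised. Report stops by arm and by reason, distinguishing mattress, actiwatch, exclusion criterion and withdrawal by the representative.

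The Adverse effects and Approval sections need to be reconciled in the same amendment. The first joins its two stop criteria with an and, which read literally requires both, while the second treats resistance alone as grounds for withdrawal. The consent wording should make clear that stopping the mattress and withdrawing from measurement are separate decisions, both open to the representative.

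The cost is a few more weeks of measurement for the patients concerned, plus a small amendment to the protocol and consent wording, with the ethical review that this needs. Watches, diaries and NPI-NH raters are already in place, and recruitment was still under way when the article was written. Patients already stopped under the present wording cannot be recovered and should be counted by arm and reason.
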